#### Wear and osteolysis assessment

Wear will be determined on the routinely made conventional AP radiographs. Standard supine anteroposterior (AP) pelvic hip radiographs (with 115% magnification) will be taken. The X-rays at 6 weeks will serve as baseline, and will be compared 1, 3, 5, 7 and 10 years postoperatively. Wear will be assessed using the 2D measurement method as described by The et al.
[18]. This method has been clinical validated by RSA and corrects for projection differences of the acetabular component. It has the advantage of approximating 3D-wear measurements without the need of lateral radiographs. Periacetabular and femoral radiolucencies will be assessed according to the three zones of De Lee and Charnley
[19] and the femoral zones (especially zone 7) of Gruen et al.
[20]. The scoring will be undertaken by an independent reviewer.

#### Bone densitometry

BMD measurements will be performed using a dual energy X-ray absorptiometry (DEXA) scanner (Hologic Inc., Bedford, Mass., USA) in order to calculate BMD changes in the pelvis as suggested by Wilkinson
[21]. The contralateral normal hip will be scanned following a standard manufacturer's protocol to establish BMD in the femoral neck, trochanter, intertrochanteric, total hip and Ward's triangle sites.

#### Functional outcome

The Hip disability and Osteoarthritis Outcome Score (HOOS) will be used to assess patient-reported functional status, health-related quality of life and physical activity
[22,23]. The short questionnaire to assess health-enhancing physical activity (SQUASH) will be used to determine habitual physical activity behavior
[24]. Dutch versions of the HOOS and SQUASH will be used, as they are reliable and validated questionnaires for the Dutch THA population
[25,26]. The Harris Hip Score will be used to assess physician-reported functional status, including range of motion
[27,28].

### Sample size

It is our hypothesis that reversed hybrid total hip arthroplasties with vitamin E-stabilized polyethylene will show less polyethylene wear at 10 years compared to reversed hybrid total hip arthroplasty without the adjunction of vitamin E. In order to detect at least a clinically relevant difference in wear of 0.5 mm with a standard deviation of 0.07 mm, 63 patients are needed in each group (alpha 0.05, power 0.80). Based on previous studies we expect a drop-out rate of 15%. We therefore aim to include 75 patients in each group, thus 150 patients in total.

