### Follow-up

In this study the main outcome parameter is polyethylene wear (mm/y) 10 years postoperatively. Secondary outcome parameters are periacetabular bone mineral density, periprosthetic osteolysis, patient- and physician-reported outcome and implant survival (Table
1). Depending on the outcome parameters, measurements will take place preoperatively, 6 weeks, and 1, 3, 5, 7 and 10 years postoperatively.

**Table 1 T1:** Secondary outcome parameters

	
1.	polyethylene wear at 1, 3, 5 and 7 years postoperatively
2.	relative decrease/increase in acetabular bone mineral density (BMD) at 1 and 2 years postoperatively
3.	acetabular and proximal femoral osteolytic changes at 1, 3, 5, 7 and 10 years postoperatively
4.	patient-reported functional outcome (HOOS and SQUASH) at 6 weeks and at 1, 3, 5, 7 and 10 years postoperatively
5.	physician-reported functional outcome (Harris Hip Score) at 6 weeks and at 1, 3, 5 and 10 years postoperatively
6.	survival (number of revisions) determined at 5 and 10 years postoperatively

Other study parameters: gender, age, *BMI*, severity of arthrosis, complications, size and inclination of the cup, surgical time and intraoperative blood loss.

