#### Univariate analysis

Student’s *T*-test will be used to determine if there is a difference in wear at 10 years postoperatively between the two groups. Differences in other outcome measures (osteolytic changes, bone mineral density, HOOS, Harris Hip score, SQUASH) between the two groups will also be analyzed with a student’s *T*-test (or non-parametric equivalent in case of a skewed distribution) at different measurement points.

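### The difference, SD and 63 per group given in the sample-size paragraph are mutually inconsistent, so the 80% power claimed for the primary outcome cannot be verified

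*Protocol article*

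**What the plan says.** The Sample size section of the protocol article gives a complete calculation. It says that for a "clinically relevant difference in wear of 0.5 mm with a standard deviation of 0.07 mm, 63 patients are needed in each group", and sets "alpha 0.05, power 0.80". It then allows for 15% drop-out: "We therefore aim to include 75 patients in each group, thus 150 patients in total".

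The Univariate analysis section names the matching test, a Student's t-test, which "will be used to determine if there is a difference in wear at 10 years postoperatively between the two groups".

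The Follow-up section defines the endpoint as a rate: "In this study the main outcome parameter is polyethylene wear (mm/y) 10 years postoperatively". The sample-size inputs are in mm, with no statement of whether they are cumulative or annual. The article gives no standardised effect, second SD or other variance assumption.

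**The concern.** An SD of 0.07 mm is very small beside a difference of 0.5 mm. If both are right, the two wear distributions barely overlap and a handful of patients would separate them. A requirement of 63 per group belongs to a much smaller standardised effect, so at least one printed figure must be wrong.

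This matters because the paragraph is the only justification given for the size of the trial, and it concerns the primary outcome. The 0.5 mm is presented as the clinically relevant difference, so the 10-year result will be read against it. If the SD behind the calculation is unknown, nobody can say what power the trial has for that difference. The mismatch between mm and mm/y adds to this, because over 10 years the two scales differ by a factor of ten.

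**Working it through.** **Inputs.** From Sample size: difference 0.5 mm, SD 0.07 mm, alpha 0.05, power 0.80, 63 evaluable per group, 15% drop-out, 75 enrolled per group (1:1). From Univariate analysis: two-sample Student's t-test on 10-year wear. Sidedness is not stated. I assume two-sided and give one-sided results where they bear on the answer.

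**Formula.** With d = difference / SD, the normal approximation is n per group = 2 × (1.960 + 0.842)² / d² = 15.70 / d². Exact t-test figures come from the noncentral t distribution.

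**1. Reproducing the stated figures.**
- 63 is obtained at d = 0.5: 15.70 / 0.25 = 62.8, rounded up to 63 (t-test: 64). One-sided, d = 0.5 gives only 50 (t-test: 51), so 63 points to a two-sided calculation.
- The drop-out step is sound: 63 / 0.85 = 74.1, rounded up to 75.

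**2. The printed inputs.**
- d = 0.5 / 0.07 = 7.14, so n = 15.70 / 51.0 = 0.31, rounded up to 1 per group.
- The t-test needs 2 per group, with power 0.92 two-sided and 0.99 one-sided.
- Under the normal approximation the answer stays at 1 for one- or two-sided tests and for power of 0.80, 0.90 or 0.95. No such variant approaches 63.
- With 63 per group, power for these inputs is about 1.00.

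**3. A single decimal slip.**
- Difference 0.05 with SD 0.07: d = 0.714, n = 15.70 / 0.510 = 30.8, so 31 (t-test: 32). One-sided gives 25. With 63 per group, two-sided power would be 98%.
- Difference 0.5 with SD 0.7: the same ratio, so again 31 or 32.

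**4. Units.** If both inputs are converted together from mm over 10 years to mm/y, d does not change and neither does n. If only the difference is converted (0.5 mm / 10 y = 0.05 mm/y) and the SD is taken as 0.07 mm/y, the result is the 32 per group of step 3.

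**5. Pairs that do give 63 per group.** Solving for the unknown at n = 63, the detectable difference is 2.802 × √(2/63) × SD = 0.499 × SD.

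| Held fixed | Implied value |
|---|---|
| SD 0.07 | difference 0.035 (0.0349 normal, 0.0352 t) |
| Difference 0.5 mm | SD 1.00 mm |
| Difference 0.05 mm/y | SD 0.10 mm/y |

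The implied values in the right-hand column do not appear in the article.

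**The case against.** The strongest reply is that the inconsistency does not show that the trial is badly sized. If the source SD was about 1.0 mm, then 63 per group is right for 0.5 mm and only the SD is misprinted. If the source inputs were 0.05 mm/y with SD 0.07 mm/y, the trial has power to spare. The unit point is also secondary on its own, since a common rescaling leaves the sample size alone. All of this stands, and it limits the point to inconsistency and unverifiable power.

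A reader might go further in three ways that the article does not support.

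- One might infer that the difference is the misstated input and that the trial is really powered for 0.035. That holds only if SD 0.07 is correct, and nothing shows that it is.
- One might infer that the design targets something about 14 times smaller than stated. That ratio (0.5 / 0.035 = 14.3) takes both figures as cumulative mm. If the SD is per year, 0.035 mm/y is 0.35 mm over 10 years, and the ratio is about 1.4 (0.5 / 0.35).
- One might fear that a null result would be wrongly taken to exclude 0.5 mm. If SD 0.07 mm is right, power for 0.5 mm with 63 per group is about 1.00, so a null result would be strong evidence against such a difference.

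None of these replies makes the printed figures agree. The sentence is intact and gives every input, so this is not a matter of detail left to a fuller document.

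**Conclusion.** The point holds as an inconsistency. The stated difference, SD, alpha and power call for about 2 patients per group by t-test, against 63 stated. The 63 corresponds to a standardised effect of 0.5 under a two-sided test, an assumption supported by the fact that one-sided testing would give 50 or 51. Neither a single decimal slip nor a change of unit closes the gap.

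The article does not show which figure is wrong. What follows is that 80% power for the stated clinically relevant difference cannot be verified. It does not follow that the trial is too small or too large, or that 0.035 is the design difference. The sample-size statement for the primary outcome is nevertheless wrong as written and should be corrected.

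**What to change.** Recover the difference and SD actually used and their source. State both in the unit of the primary outcome, mm/y, with the 10-year equivalent in mm, and state the sidedness of the test. Then restate the power or detectable difference that 63 evaluable patients per group (75 enrolled) provide with those inputs.

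Until the source values are found, claim only that 63 per group gives about 80% power for a difference of 0.5 SD. Keep the clinically relevant difference as a value justified on clinical grounds. A figure worked back from the sample size should not become the benchmark for the 10-year result.

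The cost is one rewritten paragraph and possibly a different stated power or detectable difference. Whether the required number changes cannot be said until the source inputs are known.

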### Statistical analysis

#### Descriptive statistics

Descriptive statistics (means and standard deviations) will be used to describe the patient characteristics and outcome variables at the measurement points.

#### Univariate analysis

Student’s *T*-test will be used to determine if there is a difference in wear at 10 years postoperatively between the two groups. Differences in other outcome measures (osteolytic changes, bone mineral density, HOOS, Harris Hip score, SQUASH) between the two groups will also be analyzed with a student’s *T*-test (or non-parametric equivalent in case of a skewed distribution) at different measurement points.

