#### Multivariate analysis

A GEE (Generalized Estimating Equation) analysis will be used to determine whether there is a difference on the primary and secondary outcome variables between the two groups over time, adjusted for relevant covariates. A p-value of < 0.05 is considered statistically significant.

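### The stated 10-year t-test on wear, taken as written, leaves out the earlier films of patients lost or revised before year 10, can understate the difference, and is not ranked against a GEE on the same outcome

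*Protocol article*

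**What the plan says.** All references are to the Protocol article.

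- **Primary outcome (Follow-up):** "the main outcome parameter is polyethylene wear (mm/y) 10 years postoperatively". Table 1 lists wear at 1, 3, 5 and 7 years as a separate secondary outcome. Revisions are counted as another secondary outcome, at 5 and 10 years.
- **Measurement (Wear and osteolysis assessment):** "The X-rays at 6 weeks will serve as baseline, and will be compared 1, 3, 5, 7 and 10 years postoperatively".
- **First analysis (Univariate analysis):** a Student's t-test "will be used to determine if there is a difference in wear at 10 years postoperatively between the two groups". The section does not say how a cup revised before year 10 enters.
- **Second analysis (Multivariate analysis):** a GEE to determine "whether there is a difference on the primary and secondary outcome variables between the two groups over time, adjusted for relevant covariates", followed by one criterion: "A p-value of < 0.05 is considered statistically significant". Neither analysis is named as the deciding one.
- **Planned loss (Sample size):** "Based on previous studies we expect a drop-out rate of 15" per cent. The section does not say whether this includes revisions.
- **Rationale (Background):** the reaction to wear particles is described as one of the main causes of loosening, and loosening as the leading reason for revision. The investigators expect less wear and better implant survival with vitamin E.

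**The concern.** A comparison at a single late visit uses only those who reach it with the original cup in place. On the trial's own reasoning, a cup that wears fast is more likely to loosen and be revised, and this should happen more often in the control arm. Losing those cups would lower mean wear in controls more than in the study arm, so the test would lose ground exactly when the hypothesis is true. Even if losses are random, the test ignores up to four earlier films on each patient who leaves, although those films predict 10-year wear.

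The second issue is which result decides the trial. The t-test gives an unadjusted difference at 10 years; the GEE gives an adjusted difference over time. If they disagree, the article has no stated rule for settling the primary hypothesis. Nor does the GEE plainly solve the loss problem: an unweighted GEE needs loss to be unrelated to earlier wear, which is a stricter condition than a likelihood-based model needs.

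**Working it through.** **1. The plan's own sample size.** Inputs from Sample size: difference 0.5 mm, SD 0.07 mm, alpha 0.05 (taken as two-sided), power 0.80.

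n per group = 2 × (1.960 + 0.842)² × (SD/difference)² = 15.70 × (SD/difference)².

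- Stated inputs: 15.70 × (0.07/0.5)² = 0.31, so 1 per group. The stated 63 is not reproduced.
- Standardised effect 0.5 (for example 0.035/0.07): 15.70 × 4 = 62.8, so 63.
- Drop-out: 63/0.85 = 74.1, so 75. This step reproduces, and it treats a patient who drops out as contributing nothing to the primary comparison.

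The rest assumes an effect of 0.5 SD, the effect that 63 per group implies.

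**2. Effect of leaving out revised cups.** Assumptions: 10-year wear is normal with SD 1 in each arm, the study mean is 0.5 lower, 10% are lost for other reasons, and the same relation between wear and revision holds in both arms. The control revision rate is not in the article and is varied over 2, 5 and 10%.

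The extreme case, in which only the highest-wear cups are revised, has a closed form. With k the cut-off, mean wear among remaining controls is −φ(k)/Φ(k); in the study arm it is −0.5 − φ(k+0.5)/Φ(k+0.5).

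- 5% of controls revised: k = 1.645. Difference = 0.5 − 0.1086 + 0.0406 = 0.432, or 14% too small (1.6% of study cups revised).
- 8%: k = 1.405. Difference = 0.5 − 0.1616 + 0.0669 = 0.405, or 19% too small (2.8% of study cups).
- 10%: k = 1.282. Difference = 0.5 − 0.1950 + 0.0848 = 0.390, or 22% too small (3.7% of study cups).

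Weaker links, by simulation with a logistic relation (slope per SD of wear). Each cell gives the change in the difference, then the t-test power:

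| Control revision | Unrelated to wear | Slope 1 | Slope 2 | Only highest wear |
|---|---|---|---|---|
| 2% | nil, 0.82 | −1%, 0.81 | −3%, 0.81 | −6%, 0.80 |
| 5% | nil, 0.81 | −3%, 0.80 | −7%, 0.78 | −13%, 0.76 |
| 10% | nil, 0.78 | −6%, 0.77 | −13%, 0.74 | −22%, 0.70 |

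With 10% revised but no shrinkage, power would be 0.79, so most of the fall to 0.70 comes from the shrinkage.

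**3. What the earlier films would recover.** Assumptions: linear wear, true difference 0.035 mm/y, SD of patient slopes 0.068 mm/y, film error 0.15 mm, control mean about 0.10 mm/y, 12% random loss, 75 per group. The repeated-measures model is given the true covariance, which favours it.

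- Random loss only: power about 82% (t-test) against 85% (model).
- Milder revision (about 4% of control and 1% of study cups), or half of revisions wear-driven: about 76% against 84%.
- About 7 to 8% of control and 3% of study cups revised, all after observed wear above 1.1 mm at 5 years or 1.5 mm at 7 years: about 71% against 85%. The t-test estimate is 0.029 mm/y, and 0.029/0.035 = 0.83, so 17 to 18% too small. The model gives 0.035.

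**4. Two tests at 0.05.** If either could claim success, the chance of a false positive is 1 − 0.95² = 0.0975 for independent tests, 0.083 at correlation 0.7, 0.078 at 0.8 and 0.070 at 0.9. A null simulation of a 10-year t-test beside a repeated-measures group test (63 per arm, film error 0.1 to 0.4 mm) gave 0.06 to 0.08.

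**The case against.** The strongest case against has four parts.

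- **Exclusion is inferred.** A reader might conclude that the article drops revised cups; it does not say so. The mm/y label could allow a rate up to the last film before revision, and the handling of missing or revised cups may sit in a document not shown. That stands as a limit on the claim. However, the test and its time point are stated, the sample size speaks of a "clinically relevant difference in wear of 0.5 mm" in mm, and nothing written feeds earlier films into that test.
- **Bias is conditional.** A reader might infer that the trial is biased toward no difference. The documents do not support that. Bias requires revised cups to be left out, revision to be driven by wear, and more of it in controls. The Background puts aseptic loosening at 34.8-50.4% of revisions, with dislocation at 23.4-33.5% and infection at 15.0-15.8%. If only 35 to 50% of revisions are wear-driven, at total rates of about 8% and 3%, shrinkage is 5 to 8% and power 76 to 78%. This stands.
- **The plan does use earlier films.** The GEE covers the primary outcome over time. True, but it is not named as the deciding analysis.
- **The ranking can be guessed.** The main outcome, sample size and t-test all point to 10-year wear, so the GEE may be meant as supportive. This is a fair reading. A reader might also infer that type I error is already inflated; that holds only if either p-value may claim success, which the article never says. Still, the GEE sentence names the primary outcome, and one criterion covers both.

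**Conclusion.** The point holds in a conditional form. The t-test as written makes no use of planned films from patients who leave before year 10, and it can, but need not, understate the difference. Shrinkage ranges from nil to roughly 20%, the upper end needing 8 to 10% of control cups revised, all for high wear. Power falls by a few points in most cases and to about 70% at worst. A small gain from using all films (about 82% to 85%) remains even when losses are random, so the case for changing the analysis does not depend on the bias.

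These sizes rest on an assumed 0.5 SD effect and assumed revision rates. With the stated 0.5 mm and SD 0.07 mm, power would stay near 1 throughout; but those inputs do not give 63 per group, a separate matter to reconcile along with the mm and mm/y units.

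The lack of ranking is a matter of text. Its cost is an unclear deciding result, with a type I error of roughly 6 to 8% only if either test could claim success.

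**What to change.** Name one primary analysis: a likelihood-based mixed model for repeated measures on wear from all scheduled films (1, 3, 5, 7 and 10 years, each against 6 weeks), including films taken before revision, death or loss. Make the between-group difference at 10 years the primary contrast. Label the 10-year t-test and the covariate-adjusted GEE as supportive.

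No extra film or visit is needed. The cost is a change of wording and slightly more analysis work. Two consequences should be stated openly. The model assumes that loss depends only on wear already observed. For revised cups, the estimate refers to the wear that would have been seen had the cup stayed in place, so it should be read beside the revision counts already planned.

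### The 10-year wear test is valid but unadjusted: it leaves the listed age, gender and BMI data unused, and the adjusted GEE has no stated role in it

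*Protocol article*

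**What the plan says.** Under Follow-up the protocol article states that "the main outcome parameter is polyethylene wear (mm/y) 10 years postoperatively". Under Univariate analysis, a Student's t-test "will be used to determine if there is a difference in wear at 10 years postoperatively between the two groups". No covariate enters that test.

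Under Multivariate analysis, a GEE is planned for the primary and secondary outcomes. It compares the groups over time and adjusts for covariates that are called relevant but not named. The article does not say which of the two analyses decides the primary question, or whether a 10-year contrast will be taken from the GEE.

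The note to Table 1 opens with "Other study parameters: gender, age" and continues with BMI and several clinical and surgical items. The Design section names no stratification factor.

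The Sample size section assumes a "clinically relevant difference in wear of 0.5 mm with a standard deviation of 0.07 mm" and concludes that "63 patients are needed in each group" ("alpha 0.05, power 0.80"), raised to 75 per group for 15% drop-out.

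**The concern.** The trial's main endpoint is compared by a method that uses none of the patient characteristics the trial plans to record. If any of these predict wear, adjusting for them reduces the residual variance and gives a narrower interval for the same patients. It also accounts for chance differences between the arms in those variables, which allocation without named stratification factors does not prevent.

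The authors already regard some covariates as relevant to the primary outcome, since the GEE adjusts for them. The adjustment stops short of the 10-year comparison, which is the one the sample size is built on. With a ten-year horizon, enrolment cannot be reopened if drop-out exceeds the planned 15%, so precision available from data already collected has some value. At stake is efficiency, and clarity about which estimate is primary. The validity of the test is not in question.

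**Working it through.** **Inputs from the Sample size section:** difference 0.5 mm, SD 0.07 mm, alpha 0.05 (taken as two-sided; the article does not say), power 0.80, 63 per group, drop-out 15%, 75 per group enrolled. **Not in the article, so assumed:** R2, the share of variance in 10-year wear explained by age, gender and BMI, tried from 0 to 0.20.

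**Step 1: reproduce the plan's figure.** Use n per group = 2(1.960 + 0.842)² / d², where d = difference/SD and (1.960 + 0.842)² ≈ 7.849.

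- Printed inputs: d = 0.5/0.07 = 7.14, so n = 2 × 7.849 / 51.0 = 0.31, which rounds up to 1. The exact t-test needs 2 per group (power 0.92). The stated 63 does not follow.
- d = 0.5: n = 2 × 7.849 / 0.25 = 62.8, which rounds up to 63. This matches. It corresponds, for example, to 0.035 mm with SD 0.07 mm, or 0.5 mm with SD 1.0 mm.
- Drop-out: 63/0.85 = 74.1, rounded up to 75. In the other direction, 75 × 0.85 = 63.75 expected evaluable.

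The intended effect therefore appears to be 0.5 SD. That is an inference from the 63, not a printed value.

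**Step 2: effect of adjustment if d = 0.5 was intended.** Adjustment multiplies the residual SD by √(1 − R2), so d becomes 0.5/√(1 − R2). Power is from the exact two-sided t-test at 63 per group. The equivalent unadjusted sample is 63/(1 − R2).

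| Assumed R2 | √(1 − R2) | d | Power | Equivalent n per group |
|---|---|---|---|---|
| 0 | 1.000 | 0.500 | 0.795 | 63.0 |
| 0.02 | 0.990 | 0.505 | 0.803 | 64.3 |
| 0.05 | 0.975 | 0.513 | 0.815 | 66.3 |
| 0.10 | 0.949 | 0.527 | 0.835 | 70.0 |
| 0.20 | 0.894 | 0.559 | 0.876 | 78.8 |

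The first row is 0.795 rather than 0.80 only because the exact t-test replaces the normal approximation (0.801 at 63). The exact test reaches 0.801 at 64 per group.

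**Step 3: effect with the printed inputs.** At d = 7.14 and 63 per group, unadjusted power is about 1.00, so adjustment cannot add power. The 95% CI half-width is 1.979 × 0.07 × √(2/63) = 0.0247 mm. At R2 = 0.20 it would be 0.0247 × 0.894 = 0.0221 mm.

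**Step 4: the downside if R2 = 0.** Three covariates reduce the degrees of freedom from 124 to 121. The critical value moves from 1.9793 to 1.9798, and power at d = 0.5 stays at 0.795 to three decimals.

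**The case against.** The strongest reply is that nothing here is an error. Randomisation makes the unadjusted t-test unbiased, and its type I error and confidence interval already allow for chance imbalance. The sample size took no credit for covariates, so planned power is not lost. All of this stands. A reader might infer that the t-test is biased, or that imbalance would invalidate the primary result; the article does not support that.

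A second reply is that adjustment is already planned, because the GEE covers the primary outcome. This stands in part. It would be wrong to say that wear is never adjusted. But the GEE is framed as a comparison over time, and the article neither ranks it against the t-test nor ties it to year 10. The covariate list may sit in a fuller document, so its absence is not the point here.

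A third reply is that the benefit is assumed. This also stands. The article gives no R2 and does not say that age, gender or BMI predict wear. The Background says only that bearings free of polyethylene wear were increasingly used in young, active patients in particular, which makes some prognostic value plausible without sizing it. A reader might also take the table as a demonstrated power loss; it is conditional on both the assumed R2 and the inferred effect of 0.5 SD.

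A reader might further assume that preoperative SQUASH is available as a covariate. Follow-up mentions preoperative measurement in general terms, but Table 1 lists SQUASH only from 6 weeks after surgery. Nor does the article state when age and BMI are recorded, or that they will be complete.

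**Conclusion.** The point holds as an inexpensive improvement to a stated analysis choice, not as the correction of an invalid test. The 10-year comparison leaves listed patient data unused, and the adjusted analysis that exists has no defined part in it.

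The size is uncertain. If the intended effect is 0.5 SD, the gain in power at 63 per group runs from under one percentage point (R2 0.02) through two (0.05) and four (0.10) to about eight (0.20). If the printed 0.5 mm and SD 0.07 mm are taken literally, there is no power to gain and only the interval would narrow, by 1 − √(1 − R2), or about 1% to 11% over the same range. If the covariates explain nothing, the loss is negligible.

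**What to change.** Before any wear result is seen, specify one primary estimate for 10-year wear, in either of two forms:

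- a linear model of 10-year wear on arm, age, gender and BMI; or
- the between-group contrast at 10 years from the planned GEE, with the same three covariates named and the model set up so that the year-10 contrast is defined.

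Report the adjusted difference with its 95% CI and keep the t-test as a supporting analysis. Use only values recorded before randomisation, and in any case before the allocation envelope is opened. Cup size and inclination, surgical time, blood loss and complications arise later and should stay out. Add SQUASH only if a preoperative score is confirmed to be taken.

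The cost is a sentence or two in the analysis section, about three degrees of freedom, and a simple pre-stated rule for any missing baseline value. No extra patients or measurements are needed, provided the three variables are recorded before allocation.

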**Design:**

A double-blinded randomized controlled trial will be conducted. Patients to be included are aged under 70, suffer from non-inflammatory degenerative joint disease of the hip and are scheduled for a primary total hip arthroplasty. The study group will receive a reversed hybrid total hip arthroplasty with a vitamin E-stabilized highly cross-linked polyethylene cemented cup. The control group will receive a reversed hybrid total hip arthroplasty with a conventional cross-linked polyethylene cemented cup. Radiological follow-up will be assessed at 6 weeks and at 1, 3, 5, 7 and 10 years postoperatively, to determine polyethylene wear and osteolysis. Patient-reported functional status (HOOS), physician-reported functional status (Harris Hip Score) and patients’ physical activity behavior (SQUASH) will also be assessed at these intervals. Acetabular bone mineral density will be assessed by dual energy X-ray absorptiometry (DEXA) at 6 weeks and at 1 year and 2 years postoperatively. Implant survival will be determined at 10 years postoperatively.

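### Visit-by-visit tests of HOOS, SQUASH and Harris Hip Score ignore the preoperative score, which costs precision on secondary outcomes but does not bias them

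*Protocol article*

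**What the plan says.** The protocol article describes two layers of analysis.

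- **Univariate analysis.** After the t-test for wear at 10 years: "Differences in other outcome measures (osteolytic changes, bone mineral density, HOOS, Harris Hip score, SQUASH) between the two groups will also be analyzed" with a t-test, "or non-parametric equivalent in case of a skewed distribution) at different measurement points". No baseline value enters these comparisons.
- **Multivariate analysis.** A GEE is to examine the "difference on the primary and secondary outcome variables between the two groups over time, adjusted for relevant covariates". The covariates are not listed.

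On timing, Follow-up says that, according to the outcome concerned, "measurements will take place preoperatively, 6 weeks, and 1, 3, 5, 7 and 10 years postoperatively". It does not say which outcomes are taken preoperatively. Table 1 gives the three functional scores from 6 weeks onward only, and the abstract likewise ties them to the postoperative visits.

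For BMD, Table 1 defines the outcome as "relative decrease/increase in acetabular bone mineral density (BMD) at 1 and 2 years postoperatively". The abstract says: "Acetabular bone mineral density will be assessed by dual energy X-ray absorptiometry (DEXA) at 6 weeks and at 1 year and 2 years postoperatively". Bone densitometry adds that the scans are made "in order to calculate BMD changes in the pelvis".

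**The concern.** A patient's function before hip replacement usually predicts function afterwards. A two-sample test of the follow-up score leaves that predictable part in the error term, so the standard error is larger than the data require. In any one trial, a chance difference between the groups in preoperative score also carries through, in part, to the follow-up comparison.

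Precision matters here because the Background expects functional scores to be equal in the two groups. A non-significant t-test with a wide interval says little about equality; a narrower interval says more. The Discussion also plans to look at short- and mid-term function, so the visit-wise results are likely to be read in their own right.

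**Working it through.** **Step 1. Which outcomes can have a preoperative value?** Taking the outcomes in Follow-up and Table 1 in turn:

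- Wear is measured against the 6-week radiograph (Wear and osteolysis assessment).
- Acetabular BMD is first scanned at 6 weeks (abstract).
- Osteolysis around the implant and revision exist only after surgery.
- HOOS, SQUASH and Harris Hip Score can be taken before surgery.

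By elimination, the preoperative measurement of outcomes can only mean the functional scores. This is an inference, because no section states it directly.

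**Step 2. Inputs.** The article gives no figure for precision or power on function or BMD, so there is none to reproduce. From Sample size I take only the head count: 63 per group after 15% drop-out (63/0.85 = 74.1, rounded up to the stated 75). Whether 63 follows from the printed wear inputs is a separate matter and does not affect this point. The correlation r between preoperative and follow-up score is not given; I assume 0.3, 0.5 and 0.7. A true difference of 0.5 SD is used for illustration only.

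**Step 3. Formulas.** In units of the follow-up SD, with n = 63 per group:

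- Unadjusted variance of the difference: 2/n, so SE = √(2/63) = 0.178.
- Baseline-adjusted variance: (2/n)(1 − r²).
- Power for 0.5 SD: Φ(0.5/SE − 1.96). Unadjusted: 0.5/0.178 = 2.81, giving 80.1%.
- Difference detectable with 80% power: (1.96 + 0.84) × SE. Unadjusted: 0.499 SD.

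| r | Variance factor 1 − r² | Reduction | Equivalent extra patients, 1/(1 − r²) − 1 | Power for 0.5 SD | Detectable difference |
|---|---|---|---|---|---|
| unadjusted | 1 | – | – | 80.1% | 0.499 SD |
| 0.3 | 0.91 | 9% | 10% | 83.7% | 0.476 SD |
| 0.5 | 0.75 | 25% | 33% | 90.0% | 0.432 SD |
| 0.7 | 0.51 | 49% less than 1, i.e. a factor of 0.51 | 96% | 97.6% | 0.356 SD |

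The last row needs care: 1 − 0.7² = 0.51 is the variance that remains, so the reduction is r² = 49%. The figure of 51% is the remaining share.

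**Step 4. Chance imbalance.** The SE of a baseline difference is also 0.178 SD, so its 95% range is ±1.96 × 0.178 = ±0.349 SD. An imbalance at that limit moves the unadjusted follow-up difference by r × 0.349 = 0.105, 0.175 or 0.244 SD. Given that imbalance, the type I error is 7.9%, 12.9% or 20.5%. Averaged over all randomisations it remains 5%.

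**Step 5. BMD.** The outcome is already a change. With equal SDs at both scans, the change-score variance factor is 2(1 − r) and the adjusted factor is 1 − r², so their ratio is (1 + r)/2:

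- r = 0.5: 0.75, a gain of 25%
- r = 0.8: 0.90, a gain of 10%
- r = 0.9: 0.95, a gain of 5%

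The formula is for absolute change; for relative change it applies approximately, on the log scale.

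**The case against.** The strongest reply is that an adjusted analysis of the same outcomes is already planned. The article sets an unadjusted analysis beside an adjusted longitudinal one, and a condensed article may leave the covariate list to a fuller document. That stands: a reader might infer that the plan never adjusts these outcomes, and the Multivariate analysis section does not support that. Nothing there excludes the preoperative score. But the section does not alter the visit-wise tests, which the article itself fixes as t-tests or rank tests.

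A reader might also infer that chance imbalance biases the comparison. It does not. Randomisation keeps the t-test unbiased, with a 5% error rate overall; the figures in Step 4 are conditional on an unlucky imbalance.

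Nor is the 6-week BMD scan discarded. Table 1 analyses relative change, and the 6-week scan is the earliest, so it is evidently the reference. A change-score analysis is valid, and at high correlation covariate adjustment adds little.

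Finally, preoperative collection of the functional scores is not stated in Table 1 or the abstract. The elimination in Step 1 makes it a sound inference, but it remains one.

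**Conclusion.** The point holds for the three functional scores as an avoidable loss of precision on secondary outcomes. The variance of the visit-wise difference would fall to 0.91, 0.75 or 0.51 of its unadjusted value at an assumed correlation of 0.3, 0.5 or 0.7, that is by 9%, 25% or 49%. The conclusion rests on those assumed correlations, on a roughly linear relation between preoperative and follow-up score, and on the preoperative scores being collected. It does not touch the primary outcome, since wear is measured from the 6-week radiograph. For BMD any gain is smaller and optional. The 6-week scan is taken after surgery, so it is a reference value and not a true pre-treatment baseline.

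**What to change.** 1. State in Table 1 whether HOOS, SQUASH and Harris Hip Score are taken preoperatively.
2. If so, replace their visit-wise t-tests with ANCOVA on the preoperative score. Alternatively, estimate the visit-specific group differences from the planned repeated-measures model, with group-by-visit terms and the preoperative score as a named covariate, not as one of the outcome time points.
3. Name that adjusted analysis as the main one for function; unadjusted means can remain as description.
4. Optionally, add the 6-week BMD value as a covariate in the BMD comparison, and describe it as a postoperative reference.

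If the preoperative scores are collected as inferred, the cost is a change of analysis wording, with no new data and no extra patients. If they are not collected, the adjustment is not available for patients already operated on.
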